While this literature demonstrates the capacity of CB to influence M1 plasticity in a functionally relevant way, it remains unclear how this influence is mediated. In particular, the circuits within M1 that are targeted by CB are unknown. Given that previous research using TMS has shown that the activity of specific intracortical motor circuits relates to the acquisition of different motor skills [15], identification of the M1 circuitry that is affected by CB projections may allow the targeted modification of skill acquisition. Interestingly, growing evidence suggests that late indirect (I) wave inputs on to corticospinal neurons, which represent important predictors of neuroplasticity and motor learning [15–17], may be specifically modified by changes in CB excitability. For example, application of transcranial direct current stimulation (tDCS; a NIBS paradigm that induces neuroplastic changes in brain excitability) over CB specifically modulates paired-pulse TMS measures of late I-wave excitability [18]. In addition, the effects of CB tDCS on single-pulse TMS measures of M1 excitability are only apparent when stimulation is applied with an anterior-posterior current, which specifically activates late I-wave circuits [19]. Also, changes in late I-wave circuits following motor training were observed following a CB-dependent motor task, but were absent following a task with minimal CB involvement [15].

Based on this previous literature, it appears likely that CB projections to M1 influence activity within the late I-wave circuitry. However, the nature of this influence, particularly in relation to the plasticity of these circuits, remains unclear. The aim of this exploratory study is therefore to assess how changes in CB activity influence the excitability and plasticity of I-wave generating circuits in M1. To achieve this, CB excitability will be downregulated using cathodal tDCS, whereas plasticity targeting the early and late I-wave circuits will be concurrently induced using I-wave periodicity TMS (iTMS;[20, 21]).

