### Experimental arrangement

All participants will attend the laboratory for three separate sessions, with a washout period of at least 1 week between sessions. While the experimental protocol applied within each session will be the same, the ISI used for iTMS will vary between sessions (see below & Fig 1). Furthermore, the order in which each iTMS interval is applied will be randomised between participants. As diurnal variations in cortisol can influence the neuroplastic response to TMS, all plasticity interventions will be applied after 11 am and at approximately the same time of day within each participant.

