#### Cerebellar-brain inhibition (CBI)

The strength of CB’s inhibitory influence on M1 will be assessed using CBI, a stimulation protocol involving a conditioning stimulus applied to CB 5 ms prior to a test stimulus applied to M1 [5]. In accordance with previous literature, CB stimulation will be applied using a double cone coil, with the center of the coil located 3 cm lateral and 1 cm inferior to the inion, along the line joining the inion and the external auditory meatus of the right ear. The coil current will be directed downward, resulting in an upward induced current. The intensity of CB stimulation will be set at 60% MSO [32], whereas M1 stimulation will be set at MEP_*1mV*_. The dual coil configuration of this measurement will mean that each coil will be directly connected to an individual Magstim 200^2^ stimulator. As removing the BiStim unit will result in an increase in stimulus strength, the MEP_*1mV*_ intensity will be checked prior to baseline CBI measures, and adjusted when required. Because antidromic activation of corticospinal neurons may confound measures of CBI [33], we will ensure that the CB conditioning stimulus is at least 5% MSO below the active motor threshold for the corticospinal tract [34]. Measures of CBI will be assessed at baseline, 5 mins and 30 mins post-intervention, with 15 trials recorded for each condition at each time point.

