#### I-wave periodicity repetitive TMS (iTMS)

In accordance with previous literature [21, 35], iTMS will consist of 180 pairs of stimuli applied every 5 s, resulting in a total intervention time of 15 mins. The same intensity will be used for both stimuli, adjusted to produce a response of ~ 1mV when applied as a pair. These stimuli will be applied using ISI’s of 1.5 (iTMS_*Early*_) and 4.5 ms (iTMS_*Late*_) in separate sessions. These parameters produce robust potentiation of MEP amplitude [20, 21, 35, 36]. A sham stimulation condition (iTMS_*Sham*_) that is not expected to modulate corticospinal excitability will also be applied in a third session. Within this condition, we will stimulate intervals that correspond to the transition between the peaks and troughs of facilitation that are observed within a complete SICF curve, as these are not expected to induce any changes in excitability. This will include equal repetitions of 1.8, 2.3, 3.3, 3.8 and 4.7 ms ISI’s, applied randomly and with an inter-trial jitter of 10%.

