#### Cerebellar transcranial direct current stimulation (tDCS_CB_)

A Soterix Medical 1 x 1 DC stimulator (Soterix Medical, New York, NY) will be used to apply tDCS to CB. Current will be applied through saline-soaked sponge electrodes (EASYpads, 5 x 7 cm), with the cathode positioned over the same location used for CB TMS (i.e., 3 cm lateral and 1 cm inferior to inion, contralateral to M1 TMS) and anode positioned on the skin above the right Buccinator muscle [4, 13, 37]. Stimulation will be applied at an intensity of 2 mA for 15 mins [4, 13, 37], coincident with the application of iTMS to M1. Onset and offset of stimulation will be ramped over a 30 s period prior to and following iTMS application.

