### Statistical analysis

Kolmogorov-Smirnov tests will be applied to assess data distribution prior to statistical analysis, with log transformation applied when deviations from normal are indicated. Given that all data of interest will involve repeated-measures, linear mixed-model analysis with repeated-measures (LMM_*RM*_) will be used to perform all statistical comparisons. Each model will include single trial data, and previously reported methods [38] will be used to justify inclusion of random participant intercepts and/or slopes, and to optimize and assess model fit. To ensure measures are comparable between sessions, effects of iTMS session (iTMS_*1*.*5*_, iTMS_*4*.*5*_ & iTMS_*Sham*_) on baseline measures of MEP_*1mv*_, MEP_*PA*_, MEP_*AP*_ and CBI, in addition to responses recorded at the start of the iTMS intervention, will be investigated using one-factor LMM_*RM*_, with each measurement investigated in a separate model. Furthermore, effects of iTMS session and ISI (1.5 & 4.5 ms) on baseline SICF will be assessed using two-factor LMM_*RM*_.

Changes in excitability during the intervention will be assessed by comparing values averaged over the first, middle and last 12 stimuli of the iTMS block between iTMS sessions. Changes in corticospinal excitability following the intervention will be investigated by assessing the effects of iTMS session and time (Post 5, Post 30) on baseline-normalised MEP_*1mV*_ values. Changes in coil-orientation dependent measures of I-wave excitability following the intervention will be investigated by assessing effects of iTMS session, time and coil orientation (MEP_*PA*_, MEP_*AP*_) on baseline-normalised values. Changes in SICF measures of I-wave excitability following the intervention will be investigated by assessing effects of iTMS session, time and ISI on baseline-normalised values. Changes in CBI following the intervention will be investigated by assessing the effects of iTMS session and time on baseline-normalised CBI values. For all models, investigation of main effects and interactions will be performed using custom contrasts with Bonferroni correction, and significance will be set at *P* < 0.05. Data for all models will be presented as the estimated marginal means, whereas pairwise comparisons will be presented as the estimated mean difference (EMD) and 95% confidence interval (95%CI) for the estimate, providing a non-standardised measure of effect size.

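### No planned test or confidence interval shows whether CBI, or any other baseline-normalised outcome, changed from baseline, although tDCS is the same in every session

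*Protocol article*

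**What the plan says.** The Introduction sets out the design: "CB excitability will be downregulated using cathodal tDCS, whereas plasticity targeting the early and late I-wave circuits will be concurrently induced". Under Experimental arrangement, the sessions differ in one respect only: "While the experimental protocol applied within each session will be the same, the ISI used for iTMS will vary between sessions". The tDCS section gives a single active condition ("Stimulation will be applied at an intensity of 2 mA for 15 mins"), delivered together with iTMS. The only sham is of iTMS: "A sham stimulation condition (iTMS_*Sham*_) that is not expected to modulate corticospinal excitability will also be applied in a third session".

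CBI is measured before and after: "Measures of CBI will be assessed at baseline, 5 mins and 30 mins post-intervention". Under Data analysis, every post-intervention TMS measure is then divided by its pre-intervention value and expressed as a percentage.

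The Statistical analysis section models the result: "Changes in CBI following the intervention will be investigated by assessing the effects of iTMS session and time on baseline-normalised CBI values". The levels of time are spelled out in the MEP1mV model: "assessing the effects of iTMS session and time (Post 5, Post 30". The PA/AP model adds coil orientation, and the SICF model (the primary outcome) adds ISI. Contrasts are planned for main effects and interactions, with Bonferroni correction. Estimated marginal means will be presented for all models. The 95% CI is stated for pairwise differences.

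**The concern.** If tDCS does what the study intends, CBI moves away from its baseline in all three sessions, because all three receive the same tDCS. Dividing by baseline turns the pre-intervention value into a constant 100% and removes it as a factor level. What the model can then test is whether sessions differ from each other and whether Post 5 differs from Post 30. Neither question is whether CBI changed.

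At stake is the manipulation check. Reading the results in terms of a downregulated cerebellum requires some evidence that the cerebellar pathway shifted. Under the stated plan, non-significant session and time effects on CBI are expected both when tDCS produced a uniform shift and when it produced none. The same layout leaves absolute change from baseline untested for SICF, MEP1mV and PA/AP MEPs.

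**Working it through.** **The plan's own figure.** The sample size rests on an effect size of 0.67 for SICF change due to cerebellar tDCS, with α = 0.05, power 0.90 and n = 21. The article does not name the test. Treating 0.67 as a standardised mean change in a paired t-test (noncentral t):
- one-sided: n = 21, with power 0.906 at 21, which matches;
- two-sided: n = 26, with power 0.831 at 21, which does not match.

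So the figure is consistent with a test of mean change. The planned models contain no such test.

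**Algebra.** Let m_st be the expected normalised value in session s (3 levels) at post time t (2 levels). Every contrast for session, time or session × time has the form Σ c_st m_st with Σ c_st = 0. Add a common shift δ to all six cells:

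Σ c_st (m_st + δ) = Σ c_st m_st + δ Σ c_st = Σ c_st m_st.

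The shift drops out and only the intercept changes. For example, with CBI at 130% of baseline in all six cells, each session difference is 130 − 130 = 0, Post 5 minus Post 30 is 0, and so is the interaction. Orientation and ISI contrasts also sum to zero, so a shift common to their levels cancels too.

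**Simulation.** Inputs: 21 participants × 3 sessions × 2 post times; participant-level log(post/pre); the same shift in every cell; 5,000 replicates. Assumed SDs: participant 0.20, session within participant 0.20, residual 0.15. Rejection rates at P < 0.05:

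| True value, % of baseline | Session | Time | Session × time | Grand mean against 100% (not planned) |
|---|---|---|---|---|
| 100 | 4.9% | 5.4% | 5.3% | 5.2% |
| 111 | 5.4% | 4.4% | 5.0% | 45.6% |
| 122 | 5.3% | 4.8% | 5.1% | 95.7% |
| 135 | 5.3% | 5.0% | 5.0% | 100% |
| 165 | 4.7% | 4.8% | 4.9% | 100% |

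The three planned columns stay at the nominal level for any choice of SDs, because of the algebra above. The last column does depend on the SDs.

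**Precision already available.** The documents give no SD for CBI change. Assume an SD of log change of 0.4 per session, and 21 × 3 = 63 session-level changes. The 95% CI half-width for the session-averaged change is then:
- sessions independent: 1.96 × 0.4/√63 = 0.10;
- sessions fully correlated within participant: 2.09 × 0.4/√21 = 0.18.

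Half-widths scale with the SD. At half that SD (0.2) they are 0.05 and 0.09; at one and a half times (0.6) they are 0.15 and 0.27. An illustrative rise to 130% is ln 1.3 = 0.26. An interval centred there would exclude no change at SD 0.4 under either correlation. At SD 0.6 with fully correlated sessions it would not (0.26 < 0.27).

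**The case against.** The strongest reply is that the estimate is already in the plan. The response is post as a percentage of pre, so each marginal mean is an estimated change from baseline, and a common shift would be displayed. That stands. A reader might infer that a successful and a failed manipulation would be reported identically; the article does not support this, because the presented means would differ. What is missing is any stated interval or test to judge those means against 100%.

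A second reply concerns scope. A reader might infer that every normalised model compares only sessions and post times. That is not so: SICF has the ISI factor and PA/AP the orientation factor. The Introduction's rationale is that cerebellar tDCS acts on late I-wave circuits, and such a selective effect could appear as an ISI or orientation effect. These remain relative comparisons and do not give change from baseline.

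Third, a reader might infer that iTMS potentiation is untested. Early and late iTMS are compared with sham iTMS within participants, which is better evidence of an iTMS effect than a pre-post change. The comparison of the first, middle and last 12 stimuli also addresses change within the block, although it is framed between sessions and does not measure CBI.

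Fourth, the planned regressions use CBI change. They test association between participants, which needs no mean shift and shows none.

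Fifth, equal shifts across sessions and times are an idealisation. If the effect faded by 30 minutes or depended on iTMS, the time or session term could respond, but neither would say whether CBI differed from baseline.

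Finally, a fuller analysis plan might contain the test. The article, however, fixes the factors, the levels of time and the scope of the contrasts, so the point rests on what is stated.

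**Conclusion.** The point holds for CBI: the stated analysis of change in CBI cannot detect a change common to all sessions and both post times, which is the form that the premise of downregulation implies. Rejection stays at about 5% whatever the size of such a shift; this is exact algebra and needs no assumption about variability. The gap extends to absolute change from baseline in SICF, MEP1mV and PA/AP MEPs, but not to relative effects between sessions, ISIs or orientations.

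The 30% shift, the SD of 0.4 and the simulation SDs are illustrative assumptions. They bear only on how well the added estimate would perform.

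It would go too far to say that the proposed test could show that tDCS downregulated the cerebellum. tDCS and iTMS run together and no session lacks active tDCS, so a pre-post change cannot be attributed to tDCS alone. That is a limit of the design which no analysis removes. In an exploratory study this is a point to correct before analysis, not a fatal flaw.

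**What to change.** Keep Pre as a third level of time (Pre, Post 5, Post 30) and model log values that have not been divided by baseline. For CBI, this means the conditioned response relative to the single-pulse response in the same block, at each of the three times. This form is preferable with single-trial data because it carries the error in the baseline; the between-session comparisons of change remain available as session × time contrasts.

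Alternatively, keep the normalised models and test the marginal mean of log(post/pre) against 0. Pre and post should then be averaged on the same scale: logging single trials divided by an arithmetic baseline mean gives a mean below 0 even with no change.

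In either case:
- prespecify the CBI change averaged over sessions, with its 95% CI, as the manipulation check;
- report the change within each iTMS session, with 95% CI, for SICF, MEP1mV and PA/AP MEPs;
- label all of these as uncontrolled pre-post changes that cannot be attributed to tDCS alone.

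The cost is a change of analysis wording and a few extra tests or intervals. No new data are needed.

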## Methods

### Sample size and participants

While the effects of CB tDCS on iTMS have not been previously investigated, the study by Ates and colleagues [18] investigated the influence of CB tDCS on the excitability of the I-wave generating circuits. Consequently, sample size calculations based on this study are sufficient to demonstrate the effects of activation within the pathway of interest (i.e., cerebellar projections to I-wave circuits of M1). Examination of the findings reported by Ates and colleagues revealed that changes in short-interval intracortical facilitation (SICF; paired-pulse TMS protocol indexing I-wave excitability; [22, 23]) due to CB tDCS had an effect size of 0.67. Based on the results of an *a priori* power analysis utilising this effect size, with α = 0.05 and 1-β = 0.9, we will therefore recruit 21 individuals (half female) to participate in the proposed experiment.

All participants will be recruited via advertisements placed on notice boards within the University of Adelaide, in addition to on social media platforms. Exclusion criteria will include a history of psychiatric or neurological disease, current use of medications that effect the central nervous system, or left handedness. Suitability to receive TMS will be assessed using a standard screening questionnaire [24]. The experiment will be conducted in accordance with the Declaration of Helsinki, and has been approved by the University of Adelaide Human Research Ethics Committee (approval H-2019-252). Written, informed consent will be provided prior to participation. Upon completion of the study, all data will be made fully available via hosting on the open science framework repository (https://www.cos.io/osf).

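### The single-step Bonferroni correction is valid, but a Holm step-down would detect more at the same familywise error rate wherever a family holds more than one contrast

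*Protocol article*

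**What the plan says.** The Statistical analysis section sets one follow-up rule for every model: "investigation of main effects and interactions will be performed using custom contrasts with Bonferroni correction", and "significance will be set at *P* < 0.05". No step-down procedure is named, and the contrasts that make up each family are not listed.

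The rule covers the primary outcome, change in SICF, which is modelled by "assessing effects of iTMS session, time and ISI on baseline-normalised values". That model has three sessions, two post-intervention times and two intervals. The rule also covers MEP at 1 mV, the PA and AP measures, and CBI. Pairwise results are to be shown as estimated mean differences with 95% confidence intervals. The section does not say whether those intervals are adjusted for multiplicity.

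The design is within-participant: "All participants will attend the laboratory for three separate sessions". Under Sample size and participants, the calculation is run "with α = 0.05 and 1-β = 0.9" on the finding that, in a published study, changes in SICF "due to CB tDCS had an effect size of 0.67". It concludes that "we will therefore recruit 21 individuals" and does not mention the multiplicity correction.

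**The concern.** Single-step Bonferroni tests every contrast in a family of k at 0.05/k, however many have already been rejected. Holm starts at the same threshold but relaxes it after each rejection. It controls the familywise error rate under any dependence, so it needs nothing that Bonferroni does not.

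With three sessions there is further slack. Among the three pairwise session contrasts, if one equality is false, at most one of the other two can be true. Once the smallest P value passes 0.05/3, the other two can therefore be tested at 0.05 (Shaffer's procedure).

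With 21 participants, the cost of the stricter thresholds is that a second real difference between sessions is missed more often than the stated error control requires. This matters most for a conclusion that rests on both early and late iTMS differing from sham.

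**Working it through.** **Inputs.** From the article: n = 21, effect size 0.67, alpha 0.05, planned power 0.90, three sessions.

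Assumptions:
- 0.67 is a paired standardised difference (dz) and applies to the session contrasts.
- Contrasts are two-sided.
- Mixed-model contrasts behave like participant-level paired contrasts.

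**1. The article's own figure.** For a paired t-test the noncentrality is dz × √n = 0.67 × √21 = 3.070 on 20 degrees of freedom.
- One-sided at 0.05, unadjusted (critical t 1.725): power 0.906. At n = 20 it is 0.893, so 21 is the smallest n that gives 90%. This reproduces the stated number.
- Two-sided at 0.05 (critical t 2.086): power 0.831 at n = 21. Reaching 90% would take 26.

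**2. Effect of single-step Bonferroni on one two-sided contrast at n = 21.**

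| Contrasts in family | Threshold | Power |
|---|---|---|
| 1 | 0.05 | 0.831 |
| 3 | 0.05/3 = 0.0167 | 0.675 |
| 6 | 0.05/6 = 0.0083 | 0.566 |
| 12 | 0.05/12 = 0.0042 | 0.457 |

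The rows for 6 and 12 are illustrations, since the article does not define the families.

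**3. The three procedures for three pairwise session contrasts.** Thresholds for the ordered P values are:
- Bonferroni: 0.05/3, 0.05/3, 0.05/3
- Holm: 0.05/3, 0.05/2, 0.05
- Shaffer: 0.05/3, 0.05, 0.05

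The simulation used 60,000 replicates, n = 21 and a paired-difference SD of 1. Both active sessions differ from sham by 0.67 and are equal to each other.

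| | Bonferroni | Holm | Shaffer |
|---|---|---|---|
| Power per active-versus-sham contrast, paired t | 0.675 | 0.714 | 0.763 |
| Power for both, paired t | 0.52 | 0.60 | 0.70 |
| At least one rejection, paired t | 0.83 | 0.83 | 0.83 |
| Power per contrast, pooled error | 0.72 | 0.75 | 0.79 |
| Power for both, pooled error | 0.58 | 0.65 | 0.74 |
| At least one rejection, pooled error | 0.85 | 0.85 | 0.85 |
| Familywise error, one null true, paired t | 0.018 | 0.036 | 0.049 |
| Familywise error, all nulls true, paired t | 0.045 | 0.045 | 0.045 |

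The chance of at least one rejection is the same throughout because all three procedures share the first threshold.

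**4. Sensitivity to the pattern of effects (paired t).**
- Differences from sham of 0.67 and 1.34: power for each 0.67 contrast is 0.68, 0.82 and 0.83.
- Differences from sham of 0.335 and 0.67: power for the smaller difference from sham is 0.17, 0.22 and 0.29; for the larger it is 0.68, 0.69 and 0.70.

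**The case against.** The strongest reply is that nothing here is in error. Bonferroni is valid, prespecified and transparent, and the study describes itself as exploratory. Other valid procedures exist, so the choice among them is partly preference. That stands, and it limits the point to efficiency.

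It is also fair that Bonferroni has directly matching simultaneous intervals and step-down tests do not. Holm is better for the decision to reject, not in every respect. The weight of this is limited, because the article presents its 95% intervals as a measure of effect size and does not say that they are adjusted.

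The size rests on assumptions. The 0.67 is an effect of cerebellar tDCS on SICF in another study. Here every session receives the same tDCS and only the iTMS interval differs, so a session contrast is a different quantity. In the main scenario Holm alone gains about 4 points per contrast (67.5% to 71.4%), or about 3 with pooled error. All of this stands.

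Three stronger readings are tempting and the article does not support them:
- **That Bonferroni costs power in every follow-up.** Main effects of time, ISI and coil orientation have two levels, hence one contrast each and nothing to recover.
- **That Shaffer's larger gain applies to the primary model as a whole.** It requires the family to be exactly the three pairwise session contrasts. The article speaks of custom contrasts, and follow-up of a session by time by ISI interaction may not form that family.
- **That the correction explains why 90% power is not met, or that changing it cures this.** The stated 21 corresponds to a one-sided, unadjusted test. A two-sided unadjusted contrast already has only 83%, which is a separate matter. Nor does the article say that both active-versus-sham contrasts must succeed, so 52% against 70% is not the study's power.

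**Conclusion.** The point holds as one of efficiency. For any family with more than one contrast, single-step Bonferroni is valid but less efficient for testing than Holm at the same familywise error rate. That part is general and does not depend on the effect size.

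Under the stated assumptions, and with both active sessions differing from sham by 0.67, the gain is about 4 points per contrast with Holm and 9 with Shaffer. For finding both differences it is about 8 and 18 points. In the scenarios simulated here, the per-contrast gain ranges from about 1 point for Holm on the larger of two unequal effects to about 14 points where a third, much larger contrast is rejected first. There is no gain in the chance of finding at least one difference, and in the main scenario no procedure reaches 90%. For larger families the gain depends on a definition that the article does not give.

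**What to change.** In Statistical analysis, replace the words naming the Bonferroni correction with: Holm step-down correction within each family of contrasts. Add that Shaffer's thresholds (0.05/3, 0.05, 0.05) may be used only where the family is exactly the three pairwise session contrasts. Keep the estimated mean differences and 95% confidence intervals, and label the intervals as unadjusted (per-comparison). Make the change before any results are seen.

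The cost is a line or two of wording, with no further participants or measurements. Holm can be computed by hand from the ordered P values; the article names no statistical software, so whether Shaffer is built in cannot be judged here. The downside is that an unadjusted interval may exclude zero while its step-down test is not significant. The text should warn readers of this.

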### Data analysis

Analysis of EMG data will be completed manually via visual inspection of offline recordings. For measures in resting muscle, any trials with EMG activity exceeding 25 μV in the 100 ms prior to stimulus application will be excluded from analysis. All MEPs will be measured peak-to-peak and expressed in mV. Measures of CBI will be quantified by expressing the amplitude of individual trials produced by paired-pulse stimulation as a percentage of the mean response produced by single-pulse stimulation within the same block. For baseline measures of SICF, individual trials produced by paired-pulse stimulation will be expressed as a percentage of the mean response produced by single-pulse stimulation within the same block. However, for post-intervention responses, previous work has suggested that increased facilitation following iTMS correlates with the increased response to single pulse stimulation, and that this relationship cancels the effects of iTMS on SICF if the post-intervention single-pulse MEPs are used to normalise post-intervention SICF values [21]. Consequently, prior to normalization of post-intervention SICF values, we will use linear regression analysis to assess the relationship between post-intervention single and paired-pulse responses. If the relationship is significant, individual post-intervention SICF trials will be expressed relative to the mean pre-intervention single-pulse MEP [21]. However, if the relationship is not significant, post-intervention SICF measures will be expressed relative to the single-pulse response recorded in the same block. For all TMS measures, effects of the intervention will be quantified by expressing the post-intervention responses (normalised to the relevant single-pulse response for CBI and SICF) as a percentage of the pre-intervention responses.

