Regression analyses will be used to investigate interactions between variables. Specifically, changes in CBI due to the intervention will be regressed against changes in measures of corticospinal and intracortical function in order to assess if alterations within the CB-M1 pathway contribute to plasticity effects. In addition, changes in intracortical function due to the intervention will be regressed against changes in corticospinal function in an attempt to identify if generalised changes in excitability are driven by alterations within specific circuits.

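### When SICF is normalised to the pre-intervention single pulse, regressing its change on MEP1mV change cannot show that specific circuits drive a generalised excitability change

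*Protocol article*

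**What the plan says.** All references are to the protocol article.

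- **Test pulse.** Under I-wave excitability, SICF uses a test stimulus set at MEP1mV, with 12 trials per condition and time point. Under Transcranial magnetic stimulation, the MEP1mV intensity is found over 20 trials and reapplied at 5 and 30 minutes to measure corticospinal change.
- **Baseline SICF (Data analysis).** "For baseline measures of SICF, individual trials produced by paired-pulse stimulation will be expressed as a percentage of the mean response produced by single-pulse stimulation" in the same block.
- **Post-intervention SICF (Data analysis).** A preliminary test comes first: "we will use linear regression analysis to assess the relationship between post-intervention single and paired-pulse responses". Then either "If the relationship is significant, individual post-intervention SICF trials will be expressed relative to the mean pre-intervention single-pulse MEP", or, "if the relationship is not significant, post-intervention SICF measures will be expressed relative to the single-pulse response recorded in the same block".
- **Reason given.** Earlier work is cited as showing that "increased facilitation following iTMS correlates with the increased response to single pulse stimulation", so that dividing by the post-intervention single pulse would cancel the iTMS effect on SICF.
- **Change score.** Post-intervention values are expressed "as a percentage of the pre-intervention responses".
- **Regression (Statistical analysis).** "changes in intracortical function due to the intervention will be regressed against changes in corticospinal function". The stated purpose of this step is to "identify if generalised changes in excitability are driven by alterations within specific circuits".

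**The concern.** The regression is meant to separate a circuit-specific change from a general one. That requires an SICF change score that does not itself move with general excitability. In the branch entered when the preliminary test is significant, the score does move with it. A participant whose response to the test pulse rises by 30% shows a 30% rise in SICF even if the facilitation ratio is unchanged. Across participants, this alone produces a positive slope.

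The work that the protocol cites suggests that this branch is a likely one. A significant slope would then invite the conclusion that I-wave circuits drive the generalised change, when the same slope is expected with no circuit-specific change at all.

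**Working it through.** **Algebra**

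Let S0 and S1 be the single-pulse responses before and after the intervention, P0 and P1 the paired-pulse responses, and f = P/S the facilitation ratio.

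- Branch A (preliminary test significant): SICF change = (P1/S0) / (P0/S0) = P1/P0 = (S1/S0) × (f1/f0). The corticospinal change S1/S0 is a factor of the score.
- Branch B (not significant): SICF change = (P1/S1) / (P0/S0) = (P1/P0) / (S1/S0). The corticospinal change cancels only if P scales fully with S.

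Illustration with no circuit-specific change: S0 = 1 mV, f = 1.6, S1 = 1.3 mV.

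- Full scaling: P0 = 1.6 and P1 = 1.6 × 1.3 = 2.08. Branch A gives 2.08/1.6 = 130%. Branch B gives (2.08/1.3)/1.6 = 100%.
- No scaling of the paired response: P1 = 1.6. Branch A gives 100%. Branch B gives (1.6/1.3)/1.6 = 77%.

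Branch A thus imports the general change when paired responses scale with single responses. Branch B imports its inverse when they do not. Logs do not remove this: if P1/P0 varies as (S1/S0)^b, the log of the branch B score contains (b − 1) × log(S1/S0).

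**Simulation**

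The protocol gives no error rate for this regression, so there is no figure of its own to reproduce.

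- From the documents: 21 participants, 12 SICF trials, a separate 20-trial MEP1mV block, alpha 0.05.
- Assumed: single-trial log-SD 0.5; mean corticospinal change 1.3-fold; baseline facilitation 1.6-fold (log-SD 0.25); baseline response log-SD 0.2; preliminary test and regression both run on one value per participant.
- Circuit-specific SICF change is generated independently of corticospinal change, with log-SD 0, 0.2 or 0.3. There were 4,000 simulated trials per setting.

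Significant regressions of SICF change on MEP1mV change under full scaling. Ranges run over the three circuit-change SDs, and the upper end from 0.1 upwards is the case of unchanged facilitation:

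| Between-participant log-SD of corticospinal change | Branch A always | Planned two-step rule |
|---|---|---|
| 0 | about 5% | about 5% |
| 0.1 | 9–17% | 7–14% |
| 0.2 | 38–74% | 30–66% |
| 0.3 | 75–97% | 66–95% |
| 0.4 | 92–100% | 86–99% |

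At log-SD 0.3 with circuit-change SD 0.2, the two-step rate is 94%, 81% and 58% for single-trial log-SD 0.3, 0.5 and 0.7.

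**What if paired responses scale only partly?**

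Same setting (0.3, 0.2, 0.5), with elasticity b of the paired on the single response. Entries are % significant (mean r):

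| b | Branch A | Branch B (same block) | Two-step rule |
|---|---|---|---|
| 1 | 88% (0.62) | 5% (0.00) | 81% (0.56) |
| 0.75 | 73% (0.53) | 10% (−0.17) | 65% (0.40) |
| 0.5 | 44% (0.39) | 30% (−0.32) | 46% (0.15) |
| 0.25 | 17% (0.21) | 56% (−0.43) | 47% (−0.16) |
| 0 | 4% (−0.01) | 76% (−0.52) | 65% (−0.40) |

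With no circuit-specific variation at all, the same-block rates at b = 0.75, 0.5 and 0 are 14%, 40% and 88%. Neither denominator isolates the circuit unless b is known.

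**The case against.** The best defence has four parts.

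1. **The pre-intervention denominator is deliberate and conditional.** This stands for the primary SICF model, where the aim is to detect an iTMS effect and dividing by the post-intervention single pulse could hide it. It does not carry over to a regression meant to tell a circuit change from a general one.
2. **MEP1mV appears to be a separate block, so the two sides share no measured term.** This also stands. A reader might infer that the regression is an arithmetic identity, or that it repeats the preliminary test. The documents support neither. The link is shared underlying excitability at one test intensity, and it disappears if participants do not differ in corticospinal change. The preliminary test uses post-intervention levels, not changes, and its unit of analysis is not stated. The simulation used separate blocks, and the artefact remained.
3. **The rates rest on variances that the documents do not give.** True, so the percentages are a range. The algebra does not depend on them.
4. **The study is called exploratory and the regression is secondary and cautiously worded.** That limits the stakes, but the stated purpose is still causal attribution to circuits, which the score cannot support.

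Two further readings go too far. A high rejection rate with facilitation unchanged is not the probability that a significant result is false; that also depends on whether facilitation really changes. Nor is same-block normalisation a cure without drawbacks, as the second table shows.

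**Conclusion.** The point holds for SICF change normalised to the pre-intervention single pulse. In that branch, a positive slope on MEP1mV change does not distinguish a circuit-specific alteration from a general one. Under full scaling, the planned two-step rule produces significant slopes at about the nominal 5% if participants do not differ in corticospinal change, and at up to 86–99% if the log-SD is 0.4. How far it departs from 5% in this trial depends on that SD, on single-trial noise and on the scaling of paired responses, none of which the documents give.

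The normalisation problem does not reach MEP_PA or MEP_AP, which are not divided by a single-pulse response. It does not affect the primary SICF comparison across session, time and ISI, which does not use this regression. A change is worth making because the normalisation rule and the regression are both fixed in the text and together would support an unwarranted mechanistic conclusion.

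**What to change.** - Keep the Data analysis normalisation rule for the primary SICF model.
- In the regressions of the Statistical analysis section, do not treat SICF change normalised to the pre-intervention single pulse as a circuit-specific measure. Use same-block-normalised change on the log scale: log(P1/S1) − log(P0/S0).
- Show the pre-normalised version, log(P1/P0), beside it as a sensitivity analysis.
- Replace the causal wording about what drives generalised changes with wording about association.
- State the limits in advance. Same-block normalisation may cancel part of a real iTMS effect, as the protocol itself notes. It also gives a negative slope if paired responses scale less than proportionally with single-pulse responses, so a negative slope must not be read as circuit-specific either.

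The cost is analysis wording and one extra set of regressions, with no new data, sessions or participants. The price is a weaker mechanistic claim and possibly less sensitivity to a real SICF effect in these regressions.
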